**Weeks 1-3:**

Target number of sit to stands per session = ½ x [4 x (Number of sit to stands done in 30 seconds +1)]

**Weeks 4-6:**

Target number of sit to stands per session = 4 x (Number of sit to stands done in 30 seconds +1)

Table 1 outlines the calculated target numbers of sit to stands for the present study.

**Table 1. Target Numbers of Sit to Stands**

| **Number of**  **Sit to Stands**  **done in 30 seconds**  **at Baseline (n)** | **Initial Target Number**  **of Sit to Stands**  **per Intervention Session**  **(Weeks 1-3)** | **Progressed Target Number**  **of Sit to Stands**  **per Intervention Session**  **(Week 4-6)** |
| --- | --- | --- |
| 1 | 4 | 8 |
| 2 | 6 | 12 |
| 3 | 8 | 16 |
| 4 | 10 | 20 |
| 5 | 12 | 24 |
| n | ½ x [4 x (n+1)] | 4 x (n+1) |

In keeping with patient-centered principles, the participant can perform all sit to stands at the beginning of the session, at the end of the session, or throughout the session according to their preference. The number of sit to stands done will be recorded by the interventionist after each session.

**Component 3:** Walking Program. Based on the findings from the patient-centered assessment interviews as well as the performance of the participants on the 2MWT at baseline (Time 1), an individualized walking program will be carried out with participants, in a manner similar to the process done in the study by Chu and colleagues (35). The goal will be to walk up to 30 minutes each session, five days per week. The interventionist will personalize the dose duration and speed of each walking session as tolerated by the participant (35) and as assessed using the Borg Rate of Perceived Exertion (RPE) scale (85, 86).

The Borg Rate of Perceived Exertion (RPE) scale (38, 39) (Appendix I) will be used during the study as used in a previous study involving walking interventions and older adults with dementia (Personal communication with [name], January 20, 2023 (35)). The RPE will be used to determine if the interventionist should continue the walk with the older adult participant, when to take breaks, or if it is time to stop. The goal will be to reach a moderate level of intensity (somewhat hard; RPE score of 13) (87) as has been used in a previous study involving an exercise intervention in older adults with CI (88). The RPE reached by each participant and the number of breaks taken at each session will also be recorded by the interventionist.

During the walk, the interventionist will engage the older adults in conversation about topics that are meaningful and interesting to them, as determined in the individualized patient-centered communication care plan (35). In keeping with patient-centered care principles (55), participants can engage in the walking program and perform sit to stands throughout the walk, or perform the sit to stands prior to the walk, or after the walk. The interventionist will use a calibrated wheel to measure the distance walked (in meters) and a stopwatch to measure walking duration (in minutes), as were used in a study involving older adults with dementia and a walking intervention (35).

# OUTCOME MEASURES

**Data Collection**

Demographic variables, including age, sex, gender, race/ethnicity, education, socioeconomic status, highest level of education, and number of co-morbidities will be collected before the start of the intervention (Appendix E). Data on hospital admission diagnosis and length of hospital stay prior to TCP admission will also be collected (Appendix E). Demographic data and outcome data at T1 will be obtained within the first month of the patient’s admission to the TCU.

Table 2 outlines the outcome measurement tools that will be used to assess the participants, time points at which they will be measured, and the type of statistical test that will be used to analyze the results. The total expected time for tests is 37 minutes at T1, and 29 minutes at T2 and 45 minutes at T3.

**Sex and Gender Considerations During Data Collection**

Participants’ sex (defined as a set of biological attributes; sex is usually categorized as female or male (90)) and gender (defined as socially constructed roles, behaviours, expressions, and identities of women, men, and gender diverse people; gender is usually conceptualized as a binary (woman and man) yet there is considerable diversity in how individuals understand, experience, and express it (40). Sex and gender will be assessed in the demographic questionnaire (Appendix E).

**Table 2. Outcome Measurement Tools, Time Points, and Statistical Tests**

| **Research Question**  **Number** | **Outcome (Tool)** | **Time Points** | | | | | | | | **Type of Statistical Test** |
| --- | --- | --- | --- | --- | --- | --- | --- | --- | --- | --- |
|  |  | **Pretest**  **Initial Assessment**  **(T1)** | **Weeks of Intervention** | | | | | | **Posttest (Immediately after 6-week intervention) (T3)** |  |
|  |  |  | **1** | **2** | **3** | **4**  **(T2)** | **5** | **6** |  |  |
| 1 | Recruitment Rate  (documentation) | √ |  |  |  |  |  |  |  | Descriptive statistics |
|  | Retention Rate  (documentation) | √ | √ | √ | √ | √ | √ | √ | √ | Descriptive statistics |
|  | Adherence  (checklist) |  | √ | √ | √ | √ | √ | √ |  | Descriptive statistics |
|  | Intervention Fidelity  (checklist) |  | √ | √ | √ | √ | √ | √ |  | Descriptive statistics |
| 2 | Satisfaction  (Client Satisfaction Questionnaire + 3 open ended questions) |  |  |  |  |  |  |  | √ | Descriptive statistics;  Content analysis |
| 3 | Lower extremity muscle strength (Time to perform one sit to stand) | √ |  |  |  | √ |  |  | √ | Means and SDs,  repeated measures ANOVA |
|  | Mobility  (2-minute walk test) | √ |  |  |  | √ |  |  | √ | Means and SDs, repeated measures ANOVA |
|  | Functional Status  (Barthel Index) | √ |  |  |  | √ |  |  | √ | Means and SDs,  repeated measures ANOVA |
|  | Quality of Life  (scale) | √ |  |  |  | √ |  |  | √ | Means and SDs,  repeated measures ANOVA |
| 4 | Discharge Destination  (Chart review) |  |  |  |  |  |  |  | √  (At the time of discharge from the TCU or within 60 days of admission to TCU, whichever comes first) | Descriptive statistics |

T1=time 1; T2=time 2; T3=time 3; ANOVA=analysis of variance; SDs=standard deviations.

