# RESEARCH QUESTIONS

1. What is the feasibility of implementing the OASIS Walking Intervention in community-dwelling older adults with CI in facility-based TCPs, as determined by recruitment rate, retention rate, and adherence?

2. What is the satisfaction of older adults with CI with the OASIS Walking Intervention?

3. Does the OASIS Walking Intervention result in improved muscle strength, mobility, functional status, and quality of life in older adults with CI?

4. What percentage of the participants are discharged home and how many are discharged to the nursing home post intervention?

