## Setting

Transitional Care Unit (TCU) in Abbeylawn Retirement home in Pickering, Ontario and TCU in Cedarbrook Lodge Retirement Home in Scarborough Ontario. The Abbeylawn TCU admits patients designated as ALC and are destined to go to long-term care and has a 35-bed capacity. From December 2023-May 2024 (or, for 6 months from the actual start date of the study), patients will be enrolled in the study on an ongoing basis. Up to 8 patients will be enrolled in the study at a given time.

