# DESCRIPTION OF INTERVENTION

**Description of the OASIS Walking Intervention**

The Older Adults with cognitive impairment performing the Sit to Stands and Walking Intervention is a nurse-led intervention that consists of three components: 1) Patient-Centered Communication Care Plan (informed by interviews with the participant and their care partner); 2) Sit to Stand Activity; and 3) Walking program (Figure 4). This intervention is grounded using a patient centered approach. An intervention manual has been created for this study (Appendix B).

Prior to the in-person sessions involving sit to stand activity and walking, the interventionist will review the participant’s medical chart and will conduct interviews with the participant and their care partner. The care partner can be their SDM, a family member, or friend, as determined by the patient or SDM. These interviews will inform the content of the patient-centered communication care plan.

**Intervention Dose.** The dose of the intervention is: up to 45 minutes per session, five sessions per week, for six weeks. Approximately up to 30 minutes will be spent walking with the participant and up to 15 minutes will be spent performing the sit-to-stand activity. Hospitalized older adults may have some difficulty reaching a moderate intensity of dose at the onset of the study. Indeed, a gradual increase in walking distance, speed, and frequency of walking sessions was used in a similar study with good effect (35). As such, for the first two weeks, intensity and frequency of dose will be gradually increased as tolerated by the participant, until the goal dose of 30 minutes, 5 days a week is reached.

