**Secondary Outcomes**

Efficacy will be assessed using measures for muscle strength, mobility, functional status, quality of life, and discharge destination. The primary outcome for efficacy will be lower extremity **muscle strength**.

**1. Lower extremity muscle strength.** Lower extremity muscle strength will be measured using the time to perform one sit-to-stand (42, 43). Time to perform one sit-to-stand has good validity and reliability. The ability to perform one sit to stand has been used in a study involving sit-to-stand activity with older adults with dementia in nursing homes (31). Repeated observations of the sit to stand test by one observer yielded correlations of 0.89 to 0.96 (44).

Older adults who are frail, such as those who are in nursing homes, must use their arms to stand and may be unable to complete more than one sit to stand (45). For a study involving sit-to-stand activity with older adults with dementia in nursing homes, participants were asked to stand from a seated position three times, with the time to complete the sit to stand measured at the third time using a stopwatch (31, 45) (personal communication with [name] January 16, 2023). Similarly, for the present study, the interventionist or RA will ask participants to stand from a seated position three times, with the time to complete the sit to stand measured at the third time using a stopwatch (Appendix E). The interventionist and the RAs will measure the time to complete the sit to stand for participants until ≥75% interrater agreement is reached (46). Then only one RA or the interventionist will collect the rest of the outcome measures data.

**2. Mobility.** Mobility will be measured using the two-minute walk test (2MWT). The 2MWT has good validity and reliability. It has been used in studies involving older adults with dementia in nursing homes (23, 34). As well, the 2MWT has been shown to provide sufficient data to objectively quantify gait measurements, similar to the six-minute walk test (47). The 2MWT has a test-retest reliability coefficient of 0.98 (0.96–0.99) and an inter-rater reliability of 0.92 (0.86–0.96) when assessed in frail older adults with dementia (34). Distances walked for the 2MWT among older adults with dementia in nursing homes and day care centers ranged between 63.1-63.6 meters (34). The minimal detectable change (MDC), that is, the minimum change that is considered a true change in performance, for the 2MWT is 9.1 meters (34).

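### The 60-day limit on recording discharge destination runs from TCU admission and can fall before the six-week intervention ends

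*Protocol*

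**What the plan says.** Research question 4 asks: "What percentage of the participants are discharged home and how many are discharged to the nursing home post intervention". The Plan for Analysis repeats the question and answers it with percentages. Secondary Outcomes gives the item an efficacy role: "Efficacy will be assessed using measures for muscle strength, mobility, functional status, quality of life, and discharge destination".

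Three statements fix the timing:

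- Table 2 ticks discharge destination in the column headed "Posttest (Immediately after 6-week intervention) (T3", and the same cell sets the moment of recording as "At the time of discharge from the TCU or within 60 days of admission to TCU, whichever comes first".
- Outcome Measures, Data Collection: "Demographic data and outcome data at T1 will be obtained within the first month of the" patient's admission to the unit.
- Description of Intervention, Intervention Dose: the dose is "up to 45 minutes per session, five sessions per week, for six weeks".

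Two other places bear on it. Stopping rules or discontinuation criteria ends data collection at discharge but keeps a record of where the patient went. The discharge-destination paragraph under Secondary Outcomes has the interventionist obtain both the planned and the actual destination from the chart or from unit staff. Neither place gives a time limit or a later time point.

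**The concern.** The column and the research question count from the intervention. The recording rule counts from admission. The two clocks agree only for participants who start early. For someone who starts late in the permitted month and stays in the unit, the rule closes the record while sessions are still going on. No actual destination exists at that moment, so the entry can only be a plan.

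Followed as written, the rule would put two different things under one percentage: real destinations, and intentions noted part-way through treatment. This is a data-collection rule, so an analysis plan could not repair it afterwards. If the chart is not looked at after day 60, the actual destination is not in the data.

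**Working it through.** The plan states no figure of its own to reproduce here; the check is calendar arithmetic with TCU admission as day 0.

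**Inputs**

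- Latest day of recording, C = 60 (Table 2).
- Latest start, S = about 30, or 28 to 31 depending on how a month is counted (Data Collection). The first session is taken to fall on the T1 day, which is the reading kindest to the plan; any gap makes the overlap larger.
- Length of intervention, D = 6 × 7 = 42 days (Intervention Dose). Counted from the first to the last weekday session it is 5 × 7 + 5 = 40 days.

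**Step 1. End of intervention for the latest permitted start: E = S + D; overrun = E − C**

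| S | E (D = 42) | Overrun | E (D = 40) | Overrun |
|---|---|---|---|---|
| 28 | 70 | 10 | 68 | 8 |
| 30 | 72 | 12 | 70 | 10 |
| 31 | 73 | 13 | 71 | 11 |

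**Step 2. Latest start that still finishes by the limit: C − D.** 60 − 42 = day 18, or 60 − 40 = day 20. The protocol does not restrict starts to that day and does not lengthen the window for later starters.

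**Step 3. Treatment given by the limit for a day-30 start.** (60 − 30)/7 = 4.3 of the six weeks.

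**Step 4. What can be recorded for a start after day 18.** There are two cases.

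- Discharged by day 60: the actual destination is recorded at discharge, but fewer than 42 days have passed since the start, so the six weeks were not completed in the unit.
- Still in the unit at day 60: there is no actual destination yet, so only the planned one can be entered, and the intervention is still running.

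In neither case does the Table 2 rule yield an actual destination after a completed intervention.

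**Step 5. How many participants.** The protocol gives neither the distribution of start days nor the length of stay, so this is a range under stated assumptions.

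- All start by day 18: 0%.
- Starts even over the month and nobody discharged before day 60: (30 − 18)/30 = 40%, which is about 10 of 26 (0.40 × 26 = 10.4). With months of 28 and 31 days it is 10/28 = 36% and 13/31 = 42%. On the 40-day count it is 8/28 = 29%, 10/30 = 33% and 11/31 = 35%.
- Discharges before day 60 lower these figures. Starts clustered late in the month would raise them.

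**The case against.** Feasibility is the primary outcome, muscle strength is the primary efficacy outcome, and discharge destination is a secondary item described by percentages in one group of 26. No hypothesis threshold and no sample-size figure rests on it. That stands, and it limits the weight of the point.

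It can also be said that the stopping-rules section and the discharge-destination paragraph already call for tracking disposition and for the actual destination, with no 60-day limit. A reader might go further than the text and infer that actual destinations of late starters are bound to be lost, or that question 4 cannot be answered at all. The documents do not support that: staff may well keep following the chart, and participants discharged before day 60 are recorded at discharge. But the only timing rule the protocol states is the one in Table 2. Its wording takes the earlier of two dates, and the two general statements supply no later time point that would override it. The inconsistency therefore remains.

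Three other inferences should be resisted.

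- The 40% is an illustration, not an estimate. One month is an upper limit on T1 and says nothing about when patients usually start.
- A reader might conclude that a pooled percentage discharged home mainly reflects site mix, because Setting says "The Abbeylawn TCU admits patients designated as ALC and are destined to go to long-term care". The protocol gives neither the expected destinations at the second site nor the enrolment split, so no size can be put on a site effect.
- A reader might suppose that the destination planned at baseline is already collected. Table 2 has no T1 tick for this outcome, and no time is given for recording the plan.

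**Conclusion.** The point holds as an internal inconsistency of moderate weight. Table 2, the T1 window under Data Collection, the six-week duration and the wording of question 4 cannot all be met for every start the protocol permits. Participants who start after about day 18 (day 20 on the 40-day count) and remain in the unit at day 60 have their destination recorded before the intervention ends, by up to 10 to 13 days (8 to 11 on the 40-day count).

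This part rests only on figures in the protocol and on taking the first session to be no earlier than T1. The number of participants affected is unknown and may be zero. The primary feasibility outcomes and the tested efficacy outcomes are not touched.

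**What to change.** Change the Table 2 cell so that the window is tied to the intervention: record the actual destination at TCU discharge or, for those still in the unit, at a fixed number of days after T3. Keeping a limit counted from admission would require at least day 70 to 73 (28 to 31 + 42) to cover every permitted start.

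In the discharge-destination paragraph and the Plan for Analysis, state that:

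- those not yet discharged form their own category;
- planned and actual destinations are tabulated separately;
- participants discharged before completing the six weeks are flagged, because their destination precedes the intended end of treatment whichever clock is used.

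Tabulating by site is a sensible addition, given what Setting says about one of the two units. A comparison with the destination planned at T1 would also be informative, but it needs a new baseline chart item.

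The cost is one table cell, a few sentences and a somewhat later chart check for the last participants. If the last participant starts on 31 May 2024, the end of the planned enrolment period, 42 days lead to 12 July. That leaves 19 days before the end of July, the study end given in the Protocol Summary. A longer interval after T3 would extend the study slightly.

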**Primary Outcome**

**Feasibility.** will be measured through recruitment rate, retention rate, and adherence (41).

**1. Recruitment rate.** Recruitment rate will be calculated as the percentage of participants who enroll in the study out of the total number of eligible participants (23). Reasons for nonenrolment and ineligibility for the study will also be recorded. A recruitment rate of >50% is considered moderate (40).

**2. Retention rate.**  Retention rate will be calculated as the percentage of participants who complete the study (i.e., receive the full dose of the intervention and provided post-test outcome data) out of the number of participants who were enrolled (i.e., signed a consent form and provided baseline data) (41). A retention rate of ≥80% is considered high (40).

**3. Adherence.** Participants’ adherence will be determined by: 1) the number of treatment sessions attended; and 2) the level of engagement with the treatment (41). For this study, the planned number of sessions is five per week for 6 weeks for a total of 30 sessions. Thus, client adherence will be measured in two ways: 1) as a percentage: the number of sessions attended divided by the total number of sessions (30 sessions); and 2) a) the duration of each walking session, duration of each intervention session, and number of sit to stands done per session; and 2) b) the number of sit to stands done per session, divided by the goal number of sit to stands (see Table 1). Participant’s adherence to treatment will be documented by the interventionist using an adherence checklist created for this study (Appendix S) immediately after each intervention session. An adherence of ≥75% is considered high (28).

**Intervention fidelity.** Intervention fidelity will also be measured through the interventionist’s self-report of 12 intervention items (41). The percentage will be calculated as the number of items done divided by the 12 items on the intervention fidelity checklist. Immediately after each session, the interventionist will document the specific activities provided during the session using a structured checklist (Appendix S) created for this study, which includes the specific activities that were done during each session. Any safety events (such as falls) that occur during the intervention sessions will also be documented.

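### For late starters still in the TCU at day 60, Table 2 closes discharge destination before the six-week programme has ended

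*Protocol*

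**What the plan says.** Four places in the protocol bear on this.

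- **Table 2** puts discharge destination in the T3 column, the assessment that directly follows the six weeks, and times it: "At the time of discharge from the TCU or within 60 days of admission to TCU, whichever comes first".
- **Data Collection** says that "outcome data at T1 will be obtained within the first month of the patient’s admission to the TCU".
- **Intervention Dose** sets the programme at "up to 45 minutes per session, five sessions per week, for six weeks". Primary Outcome confirms that "the planned number of sessions is five per week for 6 weeks for a total of 30 sessions".
- **Research Questions**, question 4, asks: "What percentage of the participants are discharged home and how many are discharged to the nursing home post intervention". Plan for Analysis repeats the question and answers it with percentages only.

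Two other places touch on destination without giving a time limit. Stopping rules or discontinuation criteria ends data collection at discharge but keeps track of where the patient goes. The discharge destination item under Secondary Outcomes records both the planned and the actual destination.

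**The concern.** The 60 days run from TCU admission. The six weeks run from the first session, which cannot come before T1. T1 can be early or late in the first month, so day 60 can fall after the programme or during it.

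For someone still in the unit during the programme at day 60, the entry closes with no actual destination and before the intervention is complete. That is not what question 4 asks for.

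The effect falls on a particular group. Retention under Primary Outcome requires the full dose and post-test data, and data collection stops at discharge. A late starter who completes must therefore still be in the unit at T3, and so at day 60 as well. Every completer whose T3 falls after day 60 is affected, and completers are the participants for whom a post-intervention destination means most.

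**Working it through.** The plan computes no figure on this point beyond the session count, which is consistent: 5 per week × 6 weeks = 30.

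**Inputs from the protocol** (admission = day 0)

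- Latest reading of destination: day 60 (Table 2).
- Latest T1: about day 30 (Data Collection; 28 to 31 by calendar month).
- Programme length: six weeks, or 42 days (Intervention Dose). Counted from a Monday in week 1 to the Friday of week 6, it is 39 days.

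**Assumed input**

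- Gap from T1 to the first session: not stated. A chart review and interviews come before the sessions, so 0, 3 and 7 days are shown.

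**Formulas**

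- Day of T3 = T1 day + gap + programme length.
- Latest T1 with T3 by day 60 = 60 − gap − programme length.

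**Base case** (gap 0, 42 days)

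- Latest T1 in time: 60 − 42 = day 18.
- T1 on day 30: T3 = 30 + 42 = day 72, and 72 − 60 = 12 days after the window closes. With a 28-day month T3 is day 70; with a 31-day month, day 73.
- With that T1, 60 − 30 = 30 days have passed at day 60. That is 30/7 = 4.3 weeks, or about 21 of the 30 sessions.
- T1 on day 0: T3 = day 42, and the window closes 60 − 42 = 18 days after it.

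Relative to T3, then, the last possible reading runs from 18 days after to 12 days before.

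**Sensitivity to the count and the gap**

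| Gap (days) | Latest T1 in time (39 / 42 days) | T3 if T1 is on day 30 (39 / 42 days) | Share of days 1–30 that are too late (39 / 42 days) |
|---|---|---|---|
| 0 | day 21 / 18 | day 69 / 72 | 30% / 40% |
| 3 | day 18 / 15 | day 72 / 75 | 40% / 50% |
| 7 | day 14 / 11 | day 76 / 79 | 53% / 63% |

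The conflict remains under every count. The last column is (30 − latest T1)/30. It is a share of permitted T1 days. It becomes a share of participants' starts only if T1 is spread evenly over the month, and it is not a share of destinations wrongly read.

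**The case against.** The strongest reply is that the rule takes discharge or day 60, whichever is earlier. A late starter who leaves before day 60 is read at actual discharge, and no sessions are then continuing in the unit. This stands, and it limits the point to late starters who are still in the TCU at day 60. A reader might infer that every T1 after day 18 gives a premature reading, or that some 40% of destinations are wrong. The documents support neither: the one-month limit on T1 is only an upper bound, and no length of stay is given. If T1 is usually early, few or no participants are affected.

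A second reply is that disposition is tracked after discharge and a planned destination is recorded, so something will be on file. This softens the point but does not remove it. A plan noted mid-programme is not a post-intervention destination, and the protocol does not say whether the planned or the actual destination enters the percentage. If tracking is meant to go past day 60, it conflicts with Table 2.

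A third reply is that a clock from admission is defensible, since it gives everyone the same maximum time in the unit. That is fair. A reader might conclude that the 60-day clock is simply wrong, but the documents show only that it does not fit question 4 as worded. Anchoring on T3 has its own unevenness: T3 + 14 days is T1 + 56, which is day 56 to day 86 from admission with no gap.

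**Conclusion.** The point holds in a narrow form. For a participant whose T1 falls after about day 18 (day 18 to 21 with no gap, earlier with one) and who is still in the TCU at day 60, the destination window closes before T3. The shortfall is up to about 12 days with no gap and more with one. Under Table 2 such a participant has no post-intervention destination, although research question 4 asks for one.

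The conflict rests only on the protocol's own figures: 60 days, one month and six weeks. How many participants it touches cannot be derived, and any percentage is illustrative.

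The consequence is minor. Discharge destination is a secondary outcome in a one-group study, with no hypothesis, threshold or test attached. The sample size, the feasibility criteria and the repeated measures analyses do not depend on it.

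**What to change.** Change the discharge-destination entry in Table 2:

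- Read destination at TCU discharge or, for those still in the unit, at the later of day 60 and T3. A fixed short time after T3 would also serve if it fits the study end.
- Make still in the TCU a category of its own.
- Report discharges before T3 separately from those after it.

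Under the later-of rule with no gap, the last reading falls between 0 and 18 days after T3, and never before it.

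The cost is a slightly later chart look-up for late starters, and a maximum observation time from admission that is no longer the same for everyone (day 60 to about day 72 with no gap).

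The stated end of July 2024 needs a check if a fixed interval after T3 is chosen. For a T1 on 31 May, T3 is 12 July and T3 + 14 days is 26 July. That leaves 31 − 26 = 5 days for any gap before the first session; a 7-day gap would take T3 + 14 to 2 August. The later-of rule is easier to fit: with T1 on 31 May and no gap, T3 is 12 July, and day 60 is 30 July even for a patient admitted that same day.
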